### Intervention

#### Content

For this population-level randomised trial, the *Cool Little Kids *parenting intervention consists of manualised parenting group sessions as previously tested in [name]'s efficacy research [41]. Parents will receive a 'workbook' at the first parenting session that presents information on the nature of inhibition, fears, anxiety and emotional distress, and the developmental trajectory of internalising problems. Thereafter, it details instructions in exposing children to their specific triggers for emotional distress to develop reality-testing and coping skills. In addition, it presents effective ways of parenting inhibited children, and methods for parents to manage their own worries and distress. The latter component involves parents applying strategies for children to themselves, plus a section on cognitive restructuring. Parents are taught how to think more realistically to manage their own concerns, so that they can gradually introduce cognitive techniques to their children as they grow older. The manual is supplemented with extensive examples and detailed exercises. It also contains information on adult mental health problems and encourages parents to seek professional help if relevant. Families with low literacy, and culturally and linguistically diverse families, will be supported by using plain English content.

#### Process - Intervention group

The intervention includes six group sessions of 90 minutes. These sessions focus on the principles outlined in the manual. Sessions involve setting readings from the manual, scheduling and motivating implementation and practice, and trouble-shooting difficulties arising during practice at home. The first two group sessions are one week apart to ensure comprehension of materials, discuss motivation and encourage implementation of the earliest strategies. The next three sessions are at fortnightly intervals to allow parents time to implement strategies and to encounter any difficulties. The final session is a booster session four weeks later to motivate parents for their longer-term goals and incorporate strategies into broader aspects of family life.

Groups of parents (~12 individuals) with inhibited children will be offered the *Cool Little Kids *program, delivered by early childhood professionals skilled in cognitive behavioural therapy techniques and instructed in the program by accredited trainers. Parent groups will be run at one of the participating preschools, or another local venue (such as a local maternal and child health service) that is convenient and acceptable to parents.

#### Process - Control group

Families in the control arm will receive usual teaching and care from their preschool, early childhood and health services in the community. This may include advice on children's behaviour, but would not include a structured, evidence-based parenting program for temperamental inhibition or internalising problems.

### Outcome measurement

Approximately one (2012) and two (2013) years after baseline, a clinician blind to group allocation will interview parents to ascertain child internalising diagnoses (see Table 1). These interviews will be conducted by telephone, which has demonstrated validity and is less expensive than face-to-face interviews [48]. A questionnaire mailed to parents will further measure child internalising symptoms, parenting practices, parent mental health and service use.

### Sample size

The randomised trial will have a sample size of around 500 inhibited children, providing 80% power at the 5% level of significance to detect the level of reduction in internalising problems found in [name]'s prior efficacy trials, namely a 14% reduction in child internalising disorders between the intervention (50%) and control (64%) groups [41]. This sample size estimation considers an achievable attrition rate for a quality trial, allowing for up to 20% loss to follow up.

### Data analyses

Regression analyses will compare child outcomes and costs at school-entry (1 and 2 years after baseline) between the intervention and control arms using the intention-to-treat principle, where participants are analysed in the groups to which they were randomised. Logistic regression will be used for binary outcomes (presenting the percentages for each trial arm and odds ratio between them) and linear regression for continuous outcomes (presenting the mean and standard deviation for each trial arm and mean difference between them). Both unadjusted analyses and analyses adjusted for potential confounding factors determined *a priori *before randomisation (child gender, family socioeconomic level, parent mental health) will be implemented. Tests of interaction, specified *a priori*, will explore differential intervention effects for children who are higher on risk factors at baseline. In line with [name]'s second efficacy trial [40], we anticipate larger group differences might emerge for children who are higher on risk factors at baseline.

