### Allocation

After recruitment and consent, the statistician will coordinate a concealed web-based randomisation process. Computer-generated sequences of random numbers will be used to determine the trial arm status of each child. A block randomisation process, stratified for each preschool separately, will minimise the imbalance between the numbers of intervention and control participants within each preschool. After families are randomised, the study team will notify all parents by letter whether they are in the intervention or control arm, and arrange group session bookings for intervention parents. Participant allocation will be concealed to the clinician assessing diagnostic outcomes; however, the group facilitators and parents cannot be blinded to their group allocation.

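### Intervention parents are treated in groups of about 12, but the 80% power assumes independent outcomes and the named regressions have no term for parent group

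*Protocol article*

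**What the plan says.** All references are to the protocol article.

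- **Allocation:** the trial arm is determined child by child, within preschool strata: "A block randomisation process, stratified for each preschool separately, will minimise the imbalance between the numbers of intervention and control participants within each preschool". The allocation ratio is not stated.
- **Process - Intervention group:** "Groups of parents (~12 individuals) with inhibited children will be offered" the programme, in six sessions run at a preschool or other local venue. Under Process - Control group, control families receive usual care and are not grouped.
- **Sample size:** the planned size is given as "The randomised trial will have a sample size of around 500 inhibited children". The power claim attached to it is "providing 80% power at the 5% level of significance", for an effect taken from earlier work, "namely a 14% reduction in child internalising disorders between the intervention (50%) and control (64%) groups". The attrition allowance is worded as "allowing for up to 20% loss to follow up". No ICC or design effect is given.
- **Data analyses:** "Logistic regression will be used for binary outcomes (presenting the percentages for each trial arm and odds ratio between them". Continuous outcomes get a linear model, and all comparisons are by intention to treat. The models are run unadjusted and adjusted for child gender, family socioeconomic level and parent mental health. Parent group is not among the terms, and neither a random effect nor a cluster-robust variance is mentioned.

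**The concern.** This is a partially nested design: outcomes can become correlated after randomisation in one arm only. Parents in a group share a facilitator, peers and joint problem-solving. If children's outcomes are more alike within groups than between them, the intervention-arm estimate is less precise than a model for independent children reports.

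Stratifying by preschool does not remove this. It balances similarity that existed before randomisation, but not similarity created by a shared group or facilitator.

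The same regressions are named for all child outcomes and costs, so every between-arm comparison is affected. An understated standard error makes a false declaration of benefit more likely, and the Discussion ties large-scale rollout to the programme proving effective.

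**Working it through.** **Inputs from the article.** Intervention 50%, control 64%; 5% level; 80% power; 20% loss; around 500 enrolled; about 12 parents per group.

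**Assumptions.** Two-sided test and 1:1 allocation (neither is stated); ICC of 0.01, 0.02, 0.05 or 0.10 on the observed scale; 20% loss spread evenly over groups; every intervention family attends a group.

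**1. Reproduce the planned size.** The pooled two-proportion formula, with mean proportion 0.57, gives

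n per arm = [1.96·√(2·0.57·0.43) + 0.8416·√(0.50·0.50 + 0.64·0.36)]² / 0.14² = (1.372 + 0.583)² / 0.0196 = 195.1.

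That is 390 completers, and 390/0.8 = 488 enrolled, which matches around 500. The unpooled formula gives 483 enrolled and the continuity-corrected one 525. A one-sided test would give 385, well short of the stated figure. So the stated size fits a two-sided calculation for independent children, with no design effect.

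**2. Power with independence.** 500 × 0.8 = 400 analysed, or 200 per arm. SE = √[(0.2304 + 0.25)/200] = 0.0490. Power = Φ(0.14/0.0490 − 1.96) = 81.5% (81.0% with pooled null variance).

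**3. Groups.** 250/12 is about 21 groups, and 12 × 0.8 = 9.6 completers per group. The design effect applies to the intervention arm only: DE = 1 + (9.6 − 1)·ICC.

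**4. The two alternatives.**

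- *A: clustering ignored.* Under the null, the true variance divided by the assumed variance is (DE + 1)/2. True error = 2·[1 − Φ(1.96/√((DE + 1)/2))].
- *B: clustering allowed for.* SE = √[(0.2304 + 0.25·DE)/200]. Power = Φ(0.14/SE − 1.96), with error held at 5%.

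| ICC | DE | (DE + 1)/2 | A: true error of nominal 5% test | A: chance of rejecting at 50% vs 64% | True SE from B | B: power |
|---|---|---|---|---|---|---|
| 0.01 | 1.086 | 1.043 | 5.5% | 81% | 0.0501 | 80% |
| 0.02 | 1.172 | 1.086 | 6.0% | 80.5% | 0.0512 | 78% |
| 0.05 | 1.430 | 1.215 | 7.5% | 79% | 0.0542 | 73% |
| 0.10 | 1.860 | 1.430 | 10.1% | 77% | 0.0590 | 66% |

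The fifth column is Φ((0.14 − 1.96·0.0490)/SE), using the true SE from column six. At ICC 0.05 the true SE is 0.0542/0.0490 = 1.11 times the one a plain regression would report.

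**5. Sensitivity.** Using pooled null variance moves power in B by at most about half a point. With 12 analysed per group instead of 9.6, ICC 0.05 gives about 71% power in B, or 8.3% error in A. With pooled variance, power at 200 per arm drops below 80% once the ICC exceeds about 0.005 (12 per group) or 0.006 (9.6 per group).

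**The case against.** **A condensed article may leave the variance method to a fuller plan.** This stands in part. Naming logistic and linear regression does not exclude a cluster-robust variance, so too-narrow intervals follow only if the regressions are run as named. The point about power does not depend on this: the size was set under independence, and a later choice of model can correct the intervals but cannot restore the power.

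**The ICC may be small.** This stands. At 0.01 the effect is negligible: about 80% power, or 5.5% error. The direction holds for any positive ICC, but the article does not fix the size.

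**Some features offset the effect.** This also stands in part. Similarity due to preschool or area is shared by both arms and largely cancels. Leaving the strata out of the model tends to widen intervals. Families who never attend have no group exposure but stay in their arm under intention to treat. The table assumes full attendance, so its figures are high if many stay away.

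**Stronger readings to avoid.** A reader might infer that the trial suffers both losses at once, with power down to 73% or 66% and an inflated error rate. It does not: the lower power belongs to the clustered analysis, which keeps the 5% error, while the inflated error belongs to the plain analysis, whose rejection rate at 50% vs 64% barely falls (about 81% to 77%). A reader might also apply the design effect to both arms. At ICC 0.05 with 12 per group, that gives 62% power instead of 71%, and it is wrong because controls are not grouped.

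**Conclusion.** The concern holds in conditional form. The stated 80% power rests on independent outcomes and leaves almost no room for correlation within parent groups, and the analysis as described has no term for it. If such correlation exists, the trial faces one of two consequences, depending on the analysis: a nominal 5% test with a true error of about 5.5% to 10.1%, or a valid test with power of about 80% down to 66%, over assumed ICCs of 0.01 to 0.10.

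Confidence is high in the direction and in the reproduction of the sample size. It is limited in the size, which depends on an ICC that the article does not give, on 1:1 allocation and on full attendance.

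**What to change.** **Data analyses.** Allow for parent group in the intervention arm, with each control child as its own cluster. Either a partially nested mixed model or cluster-robust variance will serve, with a small-sample correction because there are only about 21 groups. The robust-variance route keeps a marginal odds ratio, which matches the arm percentages to be presented; a mixed logistic model gives a conditional one. Account for the preschool strata, so that variation shared by both arms is not attributed to parent groups. Keep non-attenders in their randomised arm under a rule set in advance, for example as singletons or in the group they were booked into.

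**Sample size.** Keep about 500. State that 80% assumes independence, and give the power over a stated ICC range and group size, for example about 73-80% for ICC 0.05 down to 0.01 with 9.6 completers per group.

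**Cost.** Changes of wording in two sections, recording of each family's parent group, slightly wider intervals and a less favourable stated power. No extra participants and no change to the programme.

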### Process evaluation

Parents and group facilitators will also be mailed questionnaires at the end of the intervention (late 2011) to evaluate the screening process and intervention, where applicable. All parents will report on perceived harms and benefits of screening. Intervention parents and group facilitators will report on intervention acceptability, extent to which components were implemented, and barriers to attendance. Group facilitators will complete a standard content checklist after each group session to record the degree to which the intervention was delivered. In addition, a research assistant will observe a random 10% of parent groups and evaluate protocol adherence using the content checklist.

### Economic Evaluation

Economic evaluation will also be conducted to determine whether population application of *Cool Little Kids *provides value for money to governments (if dissemination were publicly funded), families and society in general. Economic evaluation is a comparative technique of an intervention's costs and consequences to a comparator's costs and consequences (in this instance the control group) measured as an incremental cost-effectiveness ratio (ICER). Since the current study employs a range of outcomes, the primary study design is that of a cost-consequence analysis (CCA). Such an analysis captures all relevant study outcomes which are subsequently presented to decision-makers, allowing them to make their own trade-offs regarding which are more important than others.

Most of the study outcomes are largely clinical in nature (e.g. diagnosis of anxiety disorders, scores of the various clinical scales). This means that the majority of analyses will be cost-effectiveness analyses (CEA). While such analyses are important they have limitations in deciding whether the costs and benefits of interventions represent good value-for-money or not. Cost-utility analysis (CUA) is a form of cost-effectiveness analysis where the costs are measured in monetary terms and the consequences in a generic outcome metric capable of capturing both mortality and morbidity effects, allowing judgments regarding the 'worth' or the 'value' of interventions to be made (as well as comparisons to other interventions both within and across the different disorder/diseases). Parental utility will be measured using the Assessment of Quality of Life Scale -8 Dimension (AQoL8D) [49]. There are no existing tools to measure utility in preschool children, though as the children age measures such as the Health Utilities Index 3 (HUI) may be used [50]. Alternatively, "proxy" utilities may need to suffice as used in a recent study which modeled the efficacy credentials of the *Cool Little Kids *intervention [51]. It is because the economic analyses will be comprised of both CEA and CUA analyses, the appropriate study-frame is a cost-consequence analysis.

The underlying principle in identifying costs relevant to the economic evaluation is that the inclusion/exclusion criteria should mirror the study perspective. This economic evaluation intends to adopt a largely societal perspective, so all costs to the health sector, participants and their families as well as other sectors impacted upon by the intervention will be included. As there are no previous economic evaluations in this area, a comprehensive resource use questionnaire is proposed to capture a wide variety of resource use for both parents and children (including time costs of parents). Costs associated with the initial research, design and set-up of the intervention and the development of any program materials will be excluded, as these are largely one-off 'sunk' costs (unrecoverable past expenditures), and will not be incurred in on-going routine implementation of the intervention.

The technique of 'bootstrapping' will be used to obtain confidence intervals for cost effectiveness ratios, since parametric techniques are inappropriate for use on both skewed variables and ratios. The sensitivity of the results will also be tested against: different discounting scenario; variation in the utility weights for the children; and, differences in unit cost prices. Costs falling upon the health sector, patients or their families, the government and other sectors will be presented in total and disaggregated form.

The value of economic evaluations alongside effectiveness trials is that a comprehensive analysis of the costs and benefits at an individual level can be obtained. However, such evaluations are usually time limited and do not capture the longer term costs and benefits associated with such interventions. Modelling techniques are a valuable addition to trial based evaluations. Firstly, the longer term costs and consequences associated with interventions can be estimated, though such analyses unavoidably require some assumptions to be made (e.g. a sustained effect of the intervention beyond the duration of the trial). Secondly, modelling allows the costs and benefits at a population level to be estimated. Such information is important to decision makers who are set with the task of allocating national health care budgets and must choose between different interventions. Such modelling of the current intervention is feasible and would build upon a previous study which evaluated the population cost-effectiveness of the *Cool Little Kids *intervention [51].

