***Parent measures***				

Parenting practices	Parent Behavior Checklist (nurturing, harsh discipline) [57] Over-involved/protective parenting [10,35]	Baseline 1 & 2 years	32 8	Secondary outcome (intervention mechanism for impacting on child).

Mental health	Depression, Anxiety, Stress Scale [58]	Baseline 1 & 2 years	21	Secondary outcome (impact on parent wellbeing).

Wellbeing	SF-12 [59]	Baseline	12	Secondary outcome (economics measure).
	Assessment of Quality of Life (AQoL-8D) [49]	1 & 2 years	35	Secondary outcome (economics measure).

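### SF-12 is called a secondary outcome but is taken only at baseline, and AQoL-8D, the named parental utility measure, is taken only at follow-up, so change in parental utility cannot be formed or adjusted for on one instrument

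*Protocol article*

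**What the plan says.** Three places in the protocol article bear on this point.

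- **Table 1, Parent measures.** The first row under wellbeing reads "SF-12 [59] Baseline 12 Secondary outcome (economics measure". The second reads "Assessment of Quality of Life (AQoL-8D) [49] 1 & 2 years 35 Secondary outcome (economics measure". Each instrument has its own time point, item count and label.
- **Table 1, for comparison.** Parent mental health is listed as "Depression, Anxiety, Stress Scale [58] Baseline 1 & 2 years 21", and the parenting measures have the same three time points.
- **Economic Evaluation.** AQoL-8D is the only instrument named for parental utility: "Parental utility will be measured using the Assessment of Quality of Life Scale -8 Dimension (AQoL8D) [49". The section also states that "the economic analyses will be comprised of both CEA and CUA analyses", within an overall cost-consequence design.

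The article nowhere places AQoL-8D at baseline or SF-12 at follow-up, and it does not say how the two would be linked. The description of the follow-up questionnaire under Outcome measurement ("A questionnaire mailed to parents will further measure child internalising symptoms, parenting practices, parent mental health and service use") does not mention SF-12. The adjustment factors under Data analyses ("child gender, family socioeconomic level, parent mental health) will be implemented") do not include a baseline utility or SF-12 score.

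**The concern.** There are two separate faults.

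1. **The label.** The baseline questionnaire is mailed with the trial consent form, and randomisation follows consent. SF-12 is therefore complete before any parent is allocated. It can describe the sample or serve as a covariate, but it cannot show an effect of the programme.
2. **The schedule.** The cost-utility analysis relies on AQoL-8D for parents, and its first reading comes about a year after baseline. The process evaluation dates the end of the intervention to late 2011, and the first outcome assessment is in 2012. Any change in parental utility during delivery and the months just after it therefore falls before the first AQoL-8D score. No baseline AQoL-8D score is available to correct a chance difference between the arms.

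This is not a detail that a later analysis plan could supply. An analysis plan can choose covariates, but it cannot recover a score that was never collected. The point matters because cost-effectiveness is one of the three stated aims. The Economic Evaluation section itself says that cost-effectiveness analyses are limited in judging value for money and gives that task to cost-utility analysis. The section also says that no utility tool exists for preschool children, so parental AQoL-8D is the only utility measure that the article firmly commits to collecting.

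**Working it through.** **Step 1. Time points side by side (Table 1)**

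| Parent measure | Baseline | 1 year | 2 years | Items |
|---|---|---|---|---|
| Parenting practices | yes | yes | yes | 32 + 8 |
| Depression, Anxiety, Stress Scale | yes | yes | yes | 21 |
| SF-12 | yes | no | no | 12 |
| AQoL-8D | no | yes | yes | 35 |

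The table marks repeated measurement where it is planned. Neither economics measure has both a baseline and a follow-up value.

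**Step 2. Number of parents available**

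The article gives no figure for the precision of the utility comparison, so there is none to reproduce on this point. The number of families comes from the Sample size section. That figure reproduces: for 64% against 50%, two-sided 5% and 80% power,

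n per arm = [1.96 × √(2 × 0.57 × 0.43) + 0.8416 × √(0.64 × 0.36 + 0.50 × 0.50)]² / 0.14² = 195.1, rounded up to 196.

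That is 392 evaluable and 392 / 0.80 = 490 recruited, consistent with about 500. Taking 500 less 20% loss, split equally (equal allocation is an assumption), leaves 400, or 200 per arm.

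**Step 3. Precision of the follow-up comparison without a baseline**

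The utility SD is not in the article; 0.20 is assumed.

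- Standard error of the difference = SD × √(2/200) = 0.20 × 0.10 = 0.020
- 95% half-width = 1.96 × 0.020 = 0.039

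The half-width is proportional to the assumed SD (0.196 × SD).

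**Step 4. Precision with adjustment for a baseline on the same instrument**

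Adjustment for a baseline with correlation r multiplies the half-width by √(1 − r²). This factor does not depend on the SD. The correlation is not in the article either, so a range is shown.

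| Assumed r | √(1 − r²) | Half-width | Reduction |
|---|---|---|---|
| 0.4 | 0.917 | 0.036 | 8% |
| 0.6 | 0.800 | 0.031 | 20% |
| 0.8 | 0.600 | 0.024 | 40% |

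**Step 5. Precision with a proxy baseline already collected (SF-12)**

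| Assumed r | 1 − r² | Half-width |
|---|---|---|
| 0.3 | 0.91 | 0.037 |
| 0.5 | 0.75 | 0.034 |
| 0.7 | 0.51 | 0.028 |

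If the same-instrument correlation were 0.6 and the proxy correlation 0.5, a baseline AQoL-8D would gain 0.034 − 0.031 = 0.003 over the proxy.

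**Step 6. The first-year course**

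If parental utility were summed over time by the trapezoid rule with points at 0, 1 and 2 years, the weights would be 0.5, 1 and 0.5. The uncollected starting value then has 0.5 / 2 = 25% of the two-year weight and 50% of the first-year weight. Only the segment from year 1 to year 2 can be computed from AQoL-8D alone. These are weights in the absolute total for each arm. They are not the size of an error in the difference between arms.

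**The case against.** The strongest reply is that randomisation already protects this comparison. The expected baseline difference is zero, so comparing AQoL-8D between arms at 1 and 2 years is unbiased without any baseline. Follow-up-only comparison is also the general pattern here: all three child primary outcomes in Table 1 are taken at 1 and 2 years only. Both statements are right, and they limit the point to precision and completeness.

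Three stronger readings are tempting and not supported.

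- **That parental utility cannot be corrected for baseline at all.** It cannot be corrected on the same instrument. SF-12 and the Depression, Anxiety, Stress Scale are both collected at baseline, and either can serve as a proxy covariate. Parent mental health is already an adjustment factor under Data analyses, although that section speaks of child outcomes and costs.
- **That chance baseline imbalance feeds straight into the incremental result as an extra error.** An uncollected value cannot enter a calculation. A chance baseline difference of 0.039 with correlation 0.6 would carry 0.039 × 0.6 = 0.024 into follow-up utility, but this is part of the ordinary sampling error, whose half-width is already 0.039. The article plans bootstrap intervals for the cost-effectiveness ratios.
- **That a stated quality-adjusted life-year calculation fails.** The article speaks of cost-utility analysis and parental utility. It does not mention quality-adjusted life years or an area under the curve, so Step 6 shows only what such a calculation would lack.

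It could also be said that the role of SF-12 is a detail for the full plan. That holds for how SF-12 enters a model. It does not hold for the label or the time points, which Table 1 states outright.

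**Conclusion.** The point stands in limited form. The SF-12 label is wrong as written, because the measure precedes the intervention. The named utility instrument lacks a baseline, so change in parental utility from baseline cannot be formed, or adjusted for, on one instrument, and the first-year course is not observed.

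The randomised follow-up comparison is not biased. On an assumed SD of 0.20 and 200 per arm, the avoidable loss is a half-width of about 0.039 instead of 0.036 to 0.024, for assumed correlations of 0.4 to 0.8. Part of that loss can be recovered with the baseline measures already planned. The effect is confined to the parental component of a secondary economic evaluation. The primary outcomes, the sample size and the validity of the trial comparison are untouched.

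**What to change.** 1. **At no cost.** In Table 1, relabel SF-12 as a baseline covariate. State in advance that the comparison of AQoL-8D at 1 and 2 years will be adjusted for it. This corrects the label and recovers some precision, but it does not supply the first-year utility course.
2. **Preferably.** Collect AQoL-8D in the baseline questionnaire in place of SF-12, and adjust the follow-up comparison for it. This gives utility at all three time points on one instrument. The cost is 35 − 12 = 23 extra baseline items, with the added burden on parents at the point of consent, and one edit to Table 1 and the baseline form.

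The second option is open only while baseline forms have not yet been completed. After that, the first is what remains, and the report should say that parental utility is compared at follow-up without a same-instrument baseline.
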